### Treatment adherence

Treatment adherence will be determined in two ways. First, therapists will be asked to rate the degree of adherence to the Dia-Fit intervention by the patient on a scale of 0 to 10 at the end of the therapy. Second, patients will be asked to rate the degree to which they adhered to the different modules of the Dia-Fit treatment at the end of the therapy. Both scores will be correlated with the change score (pre-treatment versus post-treatment) on the primary outcome measure.

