### Intervention

Dia-Fit consists of blended care, a combination of assignments, information and e-mail contact delivered via an internet portal and individual face-to-face sessions with a therapist. The total duration of the intervention is five months. During these months patients get online information and assignments, have fortnightly e-mail contact with their therapist and receive five to eight face-to-face sessions. The intervention is aimed at changing cognitions and behaviours thought to maintain fatigue; these are depicted in Fig. 1. Which cognitions and behaviours are relevant and applicable for the individual patient will be determined on the basis of cut-off scores on various questionnaires filled in at baseline assessment and the clinical interview by the therapist. For each fatigue-perpetuating factor a treatment module is developed. In this way the intervention can be tailored based on the applicable factors. Patients can follow from three up to eight of the following modules:*Goals setting*. All patients receive this module. The module is the start of the Dia-Fit intervention and consists of psycho-education about fatigue in T1DM and the cognitive behavioural model of fatigue in T1DM. There will be a discussion about which modules are relevant for the patient. The patient will formulate goals of the therapy that, if attained, imply that a patient is no longer severely fatigued and no longer limited by fatigue in daily functioning.*Regulation of the sleep-wake pattern*. At baseline, patients register bedtimes, times that they get up and the time slept during the day for two consecutive weeks. This module is indicated if patients score 60 or higher on the subscale sleep of the Sickness Impact Profile 8 (SIP8) [23] and/or if their bedtime and get-up time registration shows evidence of a disrupted sleep-wake pattern. In this module the importance of a regular sleep-wake cycle is discussed. Patients are asked to maintain fixed bedtimes and get-up times and to stop sleeping or lying down during the day.*Formulating helpful fatigue-related beliefs*. This module addresses low self-efficacy with respect to fatigue, fatigue catastrophising and the tendency of patients to focus on fatigue. Dysfunctional beliefs will be reformulated and patients will practice applying helpful beliefs in their daily life. If patients score 19 or lower on the Self Efficacy Scale (SES) for fatigue [24] and/or 16 or higher on the Fatigue Catastrophising Scale (FCS) [25], they will receive this module. The tendency to focus on fatigue will be addressed if patients score 30 or higher on the Illness Management Questionnaire (IMQ) subscale focusing on symptoms [26]. Patients will learn how to shift their attention to other things instead of fatigue, such as activities or the environment. Patients will also be asked to stop talking about fatigue and to ask significant others to stop talking about fatigue.*Activity regulation and increasing the level of activity.* This module is applicable for all patients and focuses on gradually increasing activity. The physical activity pattern of patients will be assessed with an actometer at baseline. An actometer is a small device which is worn at the ankle during two consecutive weeks [27]. On the basis of the scores of the actometer, each patient will be categorised in one of the two activity patterns: relatively active or low active. The physical activity of relatively active patients varies from day to day and is often characterised by ‘all or nothing’ behaviour. Relatively active patients first learn to divide their activities more evenly across the day and week and then increase their physical activity with a graded activity program. Patients can choose to increase their physical activity level either by walking or biking. They start walking or biking at least two times a day and increase their walking or biking time step by step. Patients with a low active pattern immediately start by increasing their physical activity. After patients have increased their physical activity, they apply the same principles to social or mental activities. Only patients who experience specific problems with social or mental activities will receive these elements of the module. Patients who do not need this specific step and believe that they are able to increase their level of activity will proceed with other modules and the realisation of their goals.*Coping with pain*. This module focuses on dysfunctional cognitions regarding pain. It is assumed that catastrophising thoughts with respect to pain will make it difficult for patients to increase their activity level. Therefore, patients learn to use more helpful beliefs with respect to pain. Patients who score 55 or lower on the pain subscale of the SF36 [28] and/or 16 or higher on one of the two subscales, magnification and rumination, of the Pain Catastrophising Scale (PCS) [29] will receive this module.*Optimalisation of social support and interactions.* T1DM patients with severe fatigue can experience problems in their interactions with significant others due to a lack of understanding or support. In this module patients learn how to improve their communication with significant others about fatigue. In exercises they learn how to communicate with others about fatigue and how to be more assertive. There is also an emphasis on having more realistic expectations with respect to the reaction of others. This module is indicated if patients score 50 or higher on the subscale discrepancy and/or score 14 or higher on the subscale negative interactions of the Sonderen Social Support Inventory (SSI) [30].*Reducing diabetes-related distress*. T1DM is a chronic disease, and its management is demanding for patients. Patients can develop diabetes-related distress, for example, related to the fear of the development of medical complications, hypoglycaemia or deregulated blood glucose values. In this module patients concretise the elements of diabetes that they find stressful and learn how to better cope with these elements. The module is indicated if patients score 30 or higher on the Problem Areas in Diabetes (PAID) questionnaire [31].*Step-by-step realisation of goals*. All patients end Dia-Fit with the realisation of goals. Patients realise the preset goals and evaluate the treatment effects. Patients who work less because of their fatigue will resume work in this module. Therapists will discuss with patients how to prevent relapse.

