### Training, supervision and treatment integrity

All therapists are experienced cognitive behaviour therapists working at the ECCF. Therapists will be trained in delivering Dia-Fit. They will receive bi-weekly supervision from an experienced clinical psychologist (HK).

Treatment integrity will be determined by digitally recording all face-to-face sessions and saving all e-mail contacts of Dia-Fit. At the end of the study, 5 % of the sessions and the e-mail contacts will be randomly selected and evaluated to assess to what extent the Dia-Fit treatment was delivered according to protocol.

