### Sample size

Sample size calculation was based on the guidelines of Borm and colleagues (2007) [35] and Van Breukelen (2006) [36] for analysis of covariance (ANCOVA) in randomised controlled trials. On the primary outcome parameter, the CIS fatigue severity, we assumed a clinically relevant difference in post-treatment scores of 6 between the Dia-Fit and the waiting list condition [37]. With a power of 0.90, a two-sided alpha of 0.05 and a standard deviation of 8.6, a minimum number of 45 patients would be needed per condition when using a *t*-test. According to Borm and colleagues (2007) this number of patients can be multiplied by a ‘design factor’ when ANCOVA is used. This factor is one minus the squared correlation coefficient between baseline and second assessment of fatigue severity. As we have no data on which to base this correction, we used a conservative estimate of 1 as a factor which corresponds to a relatively low correlation between baseline and second assessment of about r = .20 (1 - .20^2^ = .96 ≈ 1). Assuming a drop-out rate of 25 %, 60 patients per condition need to be randomised (n = 120 in total).

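### Adherence is rated only at the end of therapy and then correlated with the raw CIS change, so the planned correlation can appear without any adherence effect

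*Protocol article*

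**What the plan says.** The Treatment adherence section gives a closed list: "Treatment adherence will be determined in two ways". The therapist scores adherence "by the patient on a scale of 0 to 10 at the end of the therapy". The patient rates how far "they adhered to the different modules of the Dia-Fit treatment at the end of the therapy". The analysis is then fixed: "Both scores will be correlated with the change score (pre-treatment versus post-treatment) on the primary outcome measure". The section mentions no baseline adjustment.

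Three other sections bear on this.
- **Intervention:** every patient finishes with a goal-realisation module, in which "Patients realise the preset goals and evaluate the treatment effects". The therapist's stated part in that module is different: "Therapists will discuss with patients how to prevent relapse".
- **Training, supervision and treatment integrity:** integrity is checked by "digitally recording all face-to-face sessions and saving all e-mail contacts of Dia-Fit". A random 5% is evaluated, to judge delivery according to protocol and not patient adherence.
- **Statistical analysis:** the primary comparison is an ANCOVA with the baseline score as covariate.

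**The concern.** Both adherence measures are subjective and retrospective, and they are given when the response to treatment is largely visible. A patient who feels better may recall having followed the programme well, and a therapist who sees improvement may score adherence higher. In that case the outcome drives the rating.

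The raw change score opens a second route. Change contains the baseline score, so any rating related to how fatigued the patient was at the start will also correlate with change, even if it has no relation to the post-treatment score once baseline is allowed for. The primary analysis closes this route with a covariate; the adherence correlation does not.

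This is the only adherence-outcome analysis in the article. As specified, it cannot distinguish adherence leading to improvement from improvement leading to a better rating, or from baseline severity lying behind both.

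**Working it through.** **Inputs from the protocol article.** Sample size: difference 6, SD 8.6, two-sided alpha 0.05, power 0.90, drop-out 25%, and "a relatively low correlation between baseline and second assessment of about r = .20". Table 1: CIS fatigue of at least 35 at entry. Outcome measures: scale range 8 to 56.

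**Patient numbers.** The adherence correlation has no planned figure of its own, so the numbers come from the sample size, which reproduces. The two-sample t-test needs 44.16 per arm, rounded up to 45, and 45 / 0.75 = 60 randomised per arm. I use n = 45 (completers in one arm) and n = 90 (both arms pooled, since the waiting list is treated later and has its own post-treatment CIS). The article does not say whether the arms are pooled, and n = 90 allows for no further loss on the waiting list.

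**Route 1: outcome-coloured ratings.** The critical |r| is t / sqrt(n - 2 + t²), which is 0.294 at n = 45 and 0.207 at n = 90. Simulation (20,000 runs, no true adherence effect, pre-post r = .20) gives the chance of a significant correlation. The rating's correlation with improvement is an assumed range.

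| Rating vs improvement (assumed) | n = 45 | n = 90 |
|---|---|---|
| 0 | 5% | 5% |
| 0.1 | 10% | 16% |
| 0.2 | 26% | 48% |
| 0.3 | 52% | 83% |
| 0.4 | 79% | 98% |

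Fisher's z agrees. For r = 0.3 and n = 45, atanh(0.3) × sqrt(42) = 0.3095 × 6.481 = 2.01, and Φ(2.01 - 1.96) is about 0.52.

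**Route 2: coupling of change with baseline.** For baseline SD s0, post-treatment SD s1 and correlation r,

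corr(baseline, improvement) = (s0 - r·s1) / sqrt(s0² + s1² - 2·r·s0·s1).

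- Equal SDs: this reduces to sqrt((1 - r)/2), which is 0.63 at r = .20 and 0.50 at r = .50.
- Entry at 35 or more on a scale ending at 56 is likely to narrow the baseline spread. Even a uniform spread over 35-56 has SD 21/sqrt(12) = 6.1. I assume a baseline SD of 4-6 and take 8.6 as the post-treatment SD.
- s0 = 4, r = .20: (4 - 1.72) / sqrt(16 + 73.96 - 13.76) = 2.28 / 8.73 = 0.26.
- s0 = 6, r = .20: (6 - 1.72) / sqrt(36 + 73.96 - 20.64) = 4.28 / 9.45 = 0.45.
- At r = .50 the same two SDs give -0.04 and 0.22.

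A rating that correlates 0.3 with baseline (assumed) and has no other link to outcome would then correlate with change at 0.3 × 0.63 = 0.19 with equal SDs, or 0.08 to 0.14 with the narrower baseline at r = .20.

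**What baseline adjustment does.** In the same simulation (equal SDs), adding baseline as covariate returns route 2 to about 5%. It does not close route 1: for ratings correlating 0.2 to 0.3 with improvement, a significant partial correlation remains in 17-34% of trials at n = 45 and 31-61% at n = 90.

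**The case against.** Several objections are sound.

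- A reader might infer that both raters have just evaluated the treatment effect when they rate. The Intervention section says this of patients only. The therapist's knowledge is a reasonable inference from working in the same module, and the order of rating, evaluation and CIS assessment is nowhere stated.
- A reader might infer that objective adherence data already lie on the portal. The article does not say that portal use or module completion is logged. It does say that sessions are recorded and e-mails saved, though for treatment integrity.
- Counts have their own confounding. Treatment is tailored (five to eight sessions, three to eight modules), so raw counts partly reflect how many perpetuating factors a patient has. They need a patient-specific denominator.
- Large figures are easy to produce. With 10% of rating variance assumed to come from knowledge of outcome, r is 0.32 and significance follows in about 86% of trials at n = 90, but in about 56% at n = 45. Neither the 10% nor the pooling is in the documents. The 0.63 coupling likewise needs equal SDs. The r of .20 is a cautious planning value chosen for want of data, and it refers to T0 and T1, whereas pre-treatment for the waiting list is presumably T1.
- The correlation is supportive. It is not among the stated objectives, and the article draws no dose-response conclusion from it. A simple correlation among treated patients does not contradict an ANCOVA for the randomised comparison.

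These points limit the size and wording of the concern. They do not remove it: the two end-of-therapy ratings and the unadjusted change score are what the article specifies, so this is more than detail left to an analysis plan.

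**Conclusion.** The point holds as a minor weakness in a supportive analysis. The specified correlation can arise with no adherence effect, by either of two routes.

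The size is conditional. Ratings that correlate 0.2-0.3 with improvement purely through knowledge of outcome (assumed) give a significant result in about 26-52% of trials at n = 45 and 48-83% at n = 90 if the arms are pooled. The baseline coupling is 0.63 with equal SDs at r = .20, about 0.26-0.45 if the baseline SD is 4-6 (assumed) against 8.6, and weaker still if the pre-post correlation is higher.

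The documents do not support saying that a spurious correlation will appear, that the protocol claims a dose-response relation, or that the trial's main result is at risk. The primary ANCOVA and the sample size are unaffected.

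**What to change.** 1. Relate adherence to post-treatment CIS with pre-treatment CIS as covariate, the same form as the primary analysis. Define pre-treatment as the assessment just before therapy in each arm (T0 for immediate treatment, T1 for the waiting list), and say whether the arms are pooled.
2. Add adherence measures based on records made during therapy: sessions attended and fortnightly e-mails answered, each as a proportion of those planned for that patient, taken from the recordings and saved e-mails. Use portal module completion only if it is logged. The planned number should be one recorded before the response is known, where that exists, so that the denominator does not itself reflect progress.
3. Keep the therapist and patient ratings as descriptive, and state that no dose-response conclusion will be drawn from them.

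Steps 1 and 2 belong together, because the covariate alone leaves the outcome-coloured route open.

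**Cost.** Step 1 uses data already collected and needs only a change of wording. Step 2 needs some extraction from stored records. Counts measure exposure rather than quality of engagement, and they do not prove causation either, which is why the ratings remain useful as a descriptive supplement.

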### Sample size

Sample size calculation was based on the guidelines of Borm and colleagues (2007) [35] and Van Breukelen (2006) [36] for analysis of covariance (ANCOVA) in randomised controlled trials. On the primary outcome parameter, the CIS fatigue severity, we assumed a clinically relevant difference in post-treatment scores of 6 between the Dia-Fit and the waiting list condition [37]. With a power of 0.90, a two-sided alpha of 0.05 and a standard deviation of 8.6, a minimum number of 45 patients would be needed per condition when using a *t*-test. According to Borm and colleagues (2007) this number of patients can be multiplied by a ‘design factor’ when ANCOVA is used. This factor is one minus the squared correlation coefficient between baseline and second assessment of fatigue severity. As we have no data on which to base this correction, we used a conservative estimate of 1 as a factor which corresponds to a relatively low correlation between baseline and second assessment of about r = .20 (1 - .20^2^ = .96 ≈ 1). Assuming a drop-out rate of 25 %, 60 patients per condition need to be randomised (n = 120 in total).

### Randomisation

Patients will be randomised in an equal ratio (1:1) to one of the two groups: 1) intervention group or 2) waiting list group. A computer randomisation program that is created by an independent statistical expert will be used for randomisation. Block randomisation is used with blocks of 6. Patients will be stratified into two groups: 1) patients recruited from hospitals and 2) patients recruited via media. A test assistant who is not involved in the study will do the random allocation in the presence of the patient after the baseline assessment. The researcher (JM) will also be present to plan appointments with the therapist and for the second assessment. The researcher is not blinded for treatment allocation. A researcher blinded for treatment allocation will do the statistical analysis.

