## Methods/design

### Study design

The study is a randomised controlled trial (RCT) and will be conducted at the Expert Center for Chronic Fatigue (ECCF) of the Radboud University Medical Center. Patients who are eligible to participate will be randomly allocated to either the intervention group or a waiting list group. Patients allocated to the intervention group will directly receive the Dia-Fit intervention, while patients allocated to the waiting list group will receive the Dia-Fit intervention after a waiting period of five months. Assessments are planned before and after the intervention and the waiting list period. In both conditions, patients will be assessed again at a follow-up six months after receiving the treatment (Fig. 2).

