	**Exclusion criteria**
(1)	Moderate to severe renal failure operationalised as having a glomerular filtration rate (GFR) ≤ 45
(2)	Blindness or severe visual impairment
(3)	Medical history of congestive heart failure
(4)	Medical history of a stroke in the past five years
(5)	Body mass index (BMI) ≥ 40
(6)	Wheelchair-dependent
(7)	Other concurrent psychiatric or medical comorbidity that could explain the fatigue

Patients who are eligible will receive a letter from their consultant with information about the possibility of receiving treatment for persistent fatigue in the context of this research project. Attached to the letter, patients will receive a short screening questionnaire consisting of the Checklist Individual Strength (CIS) [19] and a question about the duration of the fatigue (criteria 4 and 5 of the inclusion criteria). Patients who are interested in participating can fill in the questionnaire and send it back, together with a written consent giving permission to the researcher (JM) to contact them. Patients who have a score of 35 or higher on the subscale fatigue severity of the CIS and who indicate that they are fatigued for six months or longer will receive further information about the study, both by telephone and in writing. Patients can decide to participate in the study within a period of two weeks from the time that the researcher contacted them. If patients are willing to participate, they will be asked to give written informed consent for participation in the study. They will then be invited for a baseline assessment at the ECCF. During baseline assessment, patients fill in the Beck Depression Inventory (BDI) [20] and the Symptom Check List (SCL90) [21]. Patients with a score of 4 or higher on the BDI and/or a total score of 164 or higher on the SCL90, which is higher than the mean and two standard deviations of healthy people from the general population [21], will be screened for the presence of a psychiatric disorder using the Mini-International Neuropsychiatric Interview (M.I.N.I.) [22]. Patients will be excluded if they meet the criteria of the M.I.N.I. for: depressive episode, suicidality, (hypo-)manic episode, panic disorder, obsessive-compulsive disorder, post-traumatic stress disorder, alcohol dependence and alcohol abuse, substance dependence and substance abuse, psychotic disorders, anorexia nervosa, bulimia nervosa and/or generalised anxiety disorder.

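### One fixed block size of 6 in an open trial, with the recruiting researcher at every allocation, makes a minority of allocations predictable; varying, withheld block sizes would be a cheap improvement

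*Protocol article*

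**What the plan says.** The Randomisation section of the protocol article fixes the scheme. The ratio is equal: "Patients will be randomised in an equal ratio (1:1) to one of the two groups". The block size is a single number: "Block randomisation is used with blocks of 6". The strata are defined by recruitment source, not by hospital: "Patients will be stratified into two groups: 1) patients recruited from hospitals and 2) patients recruited via media".

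On who does what, the same section says: "A test assistant who is not involved in the study will do the random allocation in the presence of the patient after the baseline assessment". It adds that the researcher "will also be present to plan appointments with the therapist and for the second assessment", and that "The researcher is not blinded for treatment allocation". The list comes from a computer program made by an independent statistical expert, and a blinded researcher does the analysis.

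The section on recruitment and study population shows the researcher's part before consent: "Patients can decide to participate in the study within a period of two weeks from the time that the researcher contacted them". The article marks this as the same person who attends the allocation. Under Study design, the trial "will be conducted at the Expert Center for Chronic Fatigue (ECCF) of the Radboud University Medical Center". Trial status says that recruitment was still open when the article appeared.

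**The concern.** With a constant block size and a 1:1 ratio, anyone who has seen the earlier allocations in a stratum can work out how many places each arm has left in the current block. Once one arm is full, the rest of the block is known. Here one person is placed to follow both strata: allocation takes place at one centre, treatment versus waiting list cannot be masked, and the researcher sees each result. The independent program and the uninvolved assistant hide the list, but not what follows from past allocations.

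At stake is selection bias. If the next arm is foreseeable, encouragement to join or the timing of visits may depend on it, knowingly or not. The primary outcome is self-reported, and the ANCOVA adjusts only for the baseline score, so differences between arms in motivation or expectation would remain.

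**Working it through.** The article gives no figure for predictability, so there is none to reproduce.

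**Inputs**
- Ratio 1:1, block size 6, two strata (Randomisation).
- 120 patients (Sample size): 45 / (1 − 0.25) = 60 per arm. This equals 120 / 6 = 20 complete blocks; an incomplete last block in a stratum changes the results little.
- Recruitment January 2014 to February 2016, about 26 months (Trial status).
- Up to two weeks to decide after contact (Recruitment process and study population); two baseline appointments two weeks apart, then allocation (Assessments).
- Assumed, not stated: the observer knows the block size and the earlier allocations in the stratum.

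**Step 1. Full history known at the moment of allocation.** A block has 6! / (3! 3!) = 20 equally likely sequences. An allocation is certain when one arm already has its three places. The best guess is the arm with more places left.

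| Position in block | Certain | Best guess right |
|---|---|---|
| 1 | 0 % | 50 % |
| 2 | 0 % | 60 % |
| 3 | 0 % | 60 % |
| 4 | 10 % | 70 % |
| 5 | 40 % | 70 % |
| 6 | 100 % | 100 % |

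Certain: (0.1 + 0.4 + 1.0) / 6 = 1.5 / 6 = 25 %, or 0.25 × 120 = 30 patients. Guessed correctly: (0.5 + 0.6 + 0.6 + 0.7 + 0.7 + 1.0) / 6 = 4.1 / 6 = 68.3 %, or 82 of 120, against 60 by chance.

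**Step 2. How out of date the history is when enrolment can be influenced.** Accrual is 120 / 26 = about 4.6 per month. That is about 2 other allocations in the two weeks between baseline appointments and about 4 in four weeks, over both strata. The split between strata is not given. If it is equal (an assumption), about 1 and 2 of these fall in the patient's own stratum.

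**Step 3. Repeat step 1 with the last k allocations of the stratum unseen.** The values for each position move k places later in the block.

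| Unseen allocations (k) | Certain | Best guess right |
|---|---|---|
| 0 | 1.5 / 6 = 25 % | 4.1 / 6 = 68 % |
| 1 | 0.5 / 6 = 8.3 % | 3.6 / 6 = 60 % |
| 2 | 0.1 / 6 = 1.7 % | 3.4 / 6 = 57 % |
| 3 | 0 | 3.2 / 6 = 53 % |

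**Step 4. What this could do to the result (illustration only).** Suppose steering moves the expected outcome of enrolled patients by d points up or down according to the guess, and a share p of guesses is right. The bias between arms before adjustment is then 2 × (2p − 1) × d. For d = 1 point on the fatigue scale this is 0.73 points at p = 0.683, 0.40 at p = 0.60 and 0.27 at p = 0.567. These are 12 %, 7 % and 4 % of the 6-point target difference. The documents give no value for d, and it may be zero.

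**Step 5. Varying block sizes.** These results come from a simulation (1,000 runs each for 60 and 120 patients) of an observer who knows the set of sizes and the full history, but not the size of the current block.

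| Sizes | Certain | Best guess right |
|---|---|---|
| 6 only | 25 % | 68 % |
| 4, 6 | 5 to 6 % | 69 % |
| 4, 6, 8 | 2 % | 68 % |

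**The case against.** The strongest objection concerns timing. The 25 % and 68 % apply to someone with an up-to-date history at the moment of allocation, when the patient has already consented and completed baseline. What could be influenced comes earlier, and by then the history is one or more allocations short. This stands, and it is why 30 of 120 is an upper bound. The scheduling of the second baseline visit remains a route, but a narrow one.

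Four further objections:
- **Knowledge of the block size.** The article does not say that the researcher knew it during recruitment. This stands as an assumption. Publication while recruitment was open makes it plausible.
- **Eligibility.** Consultants do the medical screening, and clinic patients return the fatigue questionnaire before the researcher contacts them. The researcher therefore does not control entry alone, and the remaining routes are contact, information and timing.
- **Value of the remedy.** Varying the block sizes hardly changes guessing accuracy. This stands: the gain is in certain allocations only.
- **Detail left to a fuller protocol.** This does not answer the point, because the article states the fixed block size. It is a choice made, not an item left out.

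A reader might infer that upcoming allocations are predictable in general, or that about 30 patients were open to steering. The documents do not support either. Most allocations are not certain even with full history, and nothing shows that the researcher used, or could have used in time, what had been seen.

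**Conclusion.** The weakness is real and limited. A single fixed block size, two strata followed at one centre, and an unblinded recruiting researcher at each allocation together allow part of the sequence to be deduced. The ceiling is 25 % certain (about 30 of 120) and 68 % guessable, given a known block size and complete, current history. When enrolment could be influenced, the more realistic figures are about 8 % and 60 % with one unseen allocation in the stratum, or about 2 % and 57 % with two. The number unseen depends on the accrual rate and an assumed equal split between strata.

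This is an opportunity for selection bias, not evidence of it. It does not affect the sample size or the planned analysis. Priority is low to moderate.

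**What to change.** For the allocations still to be made, the independent statistical expert should generate a new list with randomly varying block sizes, for example 4, 6 and 8, within each stratum. The sizes should be withheld from recruiting staff and left out of publications until recruitment ends.

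The gain is a fall in certain allocations from 25 % to about 2 %, even if the set of sizes becomes known. Best-guess accuracy stays near 68 % for anyone who follows the full allocation history, and the amendment should not claim otherwise. The number of patients still to be allocated is not stated, so the total benefit cannot be given.

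The cost is one new list and a minor amendment. The largest possible imbalance at the end of the list rises from 3 to 4 per stratum (half of the largest block).

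Having the researcher join only after the patient is registered should not be offered as a remedy for predictability. Planning the therapist appointments still reveals the arm, so the allocation history stays known.
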